## Abstract

**Background:**

Tuberculosis control in sub-Saharan Africa has long been hampered by poor diagnostics and weak health systems. New molecular diagnostics, such as the Xpert® MTB/RIF assay, have the potential to improve patient outcomes. We present a cluster randomised trial designed to evaluate whether the positioning of this diagnostic system within the health system has an impact on important patient-level outcomes.

**Methods/Design:**

This pragmatic cluster randomised clinical trial compared two positioning strategies for the Xpert MTB/RIF system: centralised laboratory versus primary health care clinic. The cluster (unit of randomisation) is a 2-week time block at the trial clinic. Adult pulmonary tuberculosis suspects with confirmed human immunodeficiency virus infection and/or at high risk of multidrug-resistant tuberculosis are enrolled from the primary health care clinic. The primary outcome measure is the proportion of culture-confirmed pulmonary tuberculosis cases initiated on appropriate treatment within 30 days of initial clinic visit. Univariate logistic regression will be performed as the primary analysis using generalised estimating equations with a binomial distribution function and a logit link.

**Conclusion:**

Diagnostic research tends to focus only on performance of diagnostic tests rather than on patient-important outcomes. This trial has been designed to improve the quality of evidence around diagnostic strategies and to inform the scale-up of new tuberculosis diagnostics within public health systems in high-burden settings.

**Trial registration:**

Current Controlled Trials ISRCTN18642314; South African National Clinical Trials Registry DOH-27-0711-3568.

## Background

Control of the tuberculosis (TB) epidemic in sub-Saharan Africa is a major public health challenge [1,2]. The epidemic has been exacerbated by the co-existent explosive human immunodeficiency virus (HIV) epidemic and the emergence of drug-resistant *Mycobacterium tuberculosis* strains leading to high mortality rates [2,3]. Enshrined in Millennium Development Goal 6 and the Stop TB Partnership Global Plan 2006–2015 are the targets to reduce TB prevalence and TB mortality rates by 50% (compared to 1990) by 2015 and to eliminate TB as a public health problem by 2050 [4,5]. At current rates of progress these targets will not be achieved in sub-Saharan Africa. New interventions and improved strategies for delivery of interventions are urgently required.

TB control at present relies primarily on the diagnosis and treatment of individuals with active TB disease. Early case detection and initiation of appropriate antituberculous therapy is necessary not only to reduce mortality but also to interrupt transmission. TB microscopy (still the most common diagnostic method in use worldwide) is poorly equipped to control the current TB epidemic in sub-Saharan Africa given its poor sensitivity, particularly in HIV co-infection, and inability to detect drug resistance [6]. Additionally, the placement of diagnostics in centralised facilities distant from where patients seek care contributes to significant delays [7,8] and default [9-13] before initiation of treatment. The impact of this is illustrated most starkly in multidrug-resistant TB (MDR-TB), where delays in culture and drug susceptibility testing (DST) techniques mean that 50% of patients have died by the time their culture/DST result is available [14,15].

The development of novel molecular tools, in particular the Xpert® MTB/RIF assay, offers new opportunities to tackle these problems. This is a fully automated, closed cartridge diagnostic system that utilises hemi-nested polymerase chain reaction (PCR) and molecular beacon technology to detect the presence of *Mycobacterium tuberculosis* and rifampicin-resistant mutations directly from clinical samples in less than 2 h [16-18]. The World Health Organization (WHO) recommended the system be implemented in high-burden settings on the basis of initial data from validation and demonstration studies [19-21]. Many countries are now moving ahead with implementation and there is a need for research to address key questions in the early phase of implementation so as to inform future scale-up [21]. One critical question relates to the optimal positioning of the diagnostic system within different health systems, and this is the focus of the research study.

The primary objective is to test the hypothesis that timely initiation of appropriate TB treatment when the diagnostic system is positioned at the primary health care clinic (point of care) is different from when the diagnostic system is positioned centrally at the district hospital laboratory. Secondary objectives are:

•To evaluate the impact of Xpert MTB/RIF positioning on additional clinical outcomes (mortality, hospital admission, time to initiation of antiretroviral therapy)

•To explore the cost-effectiveness of Xpert MTB/RIF implementation at primary health care clinic level

•To compare the operational feasibility of Xpert MTB/RIF placement at the primary health care clinic level and district hospital laboratory level.

## Methods/Design

### Setting

The trial is being conducted in Hlabisa health sub-district, uMkhanyakude district, northern KwaZulu-Natal, South Africa (Figure 1). This area has an extremely high dual burden of TB and HIV: the TB notification rate for the sub-district in 2010 was 1,130/100,000; HIV seroprevalence in the adult population (≥15 years) within the Africa Centre surveillance area was 24.1% in 2010; in 2008, 76% of TB cases were associated with HIV infection [22]. In the years 2000–2006 HIV and TB accounted for 71.5% of deaths in young adults (25–49 years) in the Africa Centre surveillance area [23]. HIV and TB treatment and care are delivered at 17 primary health care (PHC) clinics through decentralised collaborative programmes. Participants are recruited from the largest PHC clinic that is situated within a small urban township in the south of the sub-district, approximately 60 km by road from the district hospital.

**Figure 1 F1:**
[figure not shown]
Maps showing location of (a) the study site and (b) primary health care clinic (trial clinic) and district hospital.

### Study design

The study is a pragmatic cluster randomised clinical trial comparing two positioning strategies for the Xpert MTB/RIF system: positioning at centralised laboratory level (district hospital laboratory) versus positioning at primary health care clinic level (point of care). The cluster (unit of randomisation) is a 2-week time block at the primary health care clinic (clinic blocks), and clusters are randomly assigned to the district hospital laboratory strategy or point-of-care strategy. The trial schema is shown in Figure 2.

**Figure 2 F2:**
[figure not shown]
Trial schema.

### Participants

Adult (≥18 years) pulmonary TB suspects with confirmed HIV infection and/or at high risk of MDR-TB are included after giving informed consent. These criteria were defined because of the high risk for mortality in these groups and prioritisation for Xpert MTB/RIF testing, in line with the WHO recommendations [20]. A TB suspect is defined for the purposes of the trial as an individual with a current cough (of any duration) with or without other symptoms. High risk of MDR-TB is defined according to national and international guidelines and incorporates the following categories: failure of the standard treatment regimen (2HRZE/4HR), failure of the re-treatment regimen (2HRZES/1HRZE/5HRE), acid-fast bacilli (AFB) smear non-conversion at month 2 or 3 of the standard or re-treatment regimen, relapse or return after default, any other previous TB (4 or more weeks of TB treatment), household contact with a known MDR-TB case, prison inmate within the last 12 months and health care worker [24,25]. Participants are excluded if they report a previous diagnosis of MDR-TB or extensively drug-resistant TB (XDR-TB), are severely unwell requiring admission to hospital, or are unable to give informed consent. Participants are recruited between the times of 0800 and 1630, Monday to Friday.

### Interventions

All participants provide two spontaneously expectorated sputum specimens on the day of enrolment (spot specimens). The first sputum specimen is submitted for Xpert MTB/RIF testing. The second specimen is submitted for Mycobacterial Growth Indicator Tube (MGIT) culture, line probe assay (LPA) ± phenotypic drug susceptibility testing (DST). In both strategies, the specimen for culture/LPA/DST is transported daily (in the afternoon) to the National Health Laboratory Service (NHLS) laboratory at the district hospital and then onwards to the provincial NHLS referral laboratory. The results of this are used to define TB cases and to define the primary outcome measure.

#### District hospital laboratory strategy

Sputum specimens are transported on a daily basis to the National Health Laboratory Service (NHLS) laboratory at the district hospital using the routine sample transport system. Xpert MTB/RIF testing is performed by a trained laboratory technician at the earliest convenience (within 24 h of the specimen being received in the laboratory) and printed results are returned to the clinic using the same routine transport system. Under this strategy, participants are requested to return for results after 72 h.

#### Point-of-care (POC) strategy

The diagnostic system is located at the primary health care in a dedicated room close to the TB clinic (Figure 3). Xpert MTB/RIF testing is performed immediately by the study nurse, on the same day where possible. Participants are invited to wait for the result (approximately 2 h) or, if they are unable to wait or it is towards the end of the working day, they are advised to return the following day.

**Figure 3 F3:**
[figure not shown]
Professional nurse operating the Xpert MTB/RIF system at the primary health care clinic.

### Outcome measures

The observational unit for all analyses is the individual participant. The primary outcome for the study is the proportion of culture-confirmed pulmonary TB cases initiated on appropriate TB treatment within 30 days of initial clinic visit (appropriate treatment defined according to results of LPA ± phenotypic DST on the culture isolate).

Secondary outcomes at an individual level are the following, with all time-to-event analyses using the initial clinic visit as time zero:

•All-cause mortality in TB suspects and MDR-TB suspects at 60 days

•Time to initiation of appropriate TB treatment (days) for culture-confirmed pulmonary TB cases

•Time to initiation of MDR-TB treatment (for MDR-TB cases confirmed by culture/LPA/DST)

•Proportion of TB suspects and MDR-TB suspects with at least one hospital attendance within 60 days

•Time to initiation of antiretroviral therapy (ART) for HIV-infected TB suspects and MDR-TB suspects not yet receiving but eligible for ART

•Sensitivity and specificity of Xpert MTB/RIF

▪ for *M. tuberculosis* detection (compared to reference standard of single MGIT culture)

▪ for detection of rifampicin resistance (compared to reference standard of phenotypic DST ± LPA)

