### Implementation

Health care workers at the primary health care clinic identify potential participants. All individuals reporting cough are referred to the study nurse. Eligibility criteria are checked by the nurse, and subjects meeting the inclusion criteria are provided spoken and written information about the study in isiZulu and/or English; those willing to participate are taken through the informed consent process and are asked to provide a signature or thumbprint on the consent form.

A baseline assessment is performed by the study nurse. Demographic information, current symptoms, previous TB history, risk factors for drug resistance, HIV status, and history of ART use are documented on a case report form.

With both strategies, clinical decisions are made by the study nurse on the basis of the Xpert MTB/RIF result and according to pre-defined algorithms. TB patients without resistance to rifampicin are commenced on standard anti-TB therapy (4HRZE/2HR) by the study nurse. All patients with rifampicin-resistant TB are reported to the trial physician on the same day and are subsequently referred to the specialist drug-resistant TB treatment centre in Durban. Management of suspects with a negative Xpert MTB/RIF follows existing protocols for smear-negative TB suspects: oral antibiotics are prescribed and patients are advised to return if symptoms do not improve after 14 days. Patients who remain symptomatic following this course of antibiotics can be referred to the district hospital for chest X-ray and physician review. Results from MGIT culture and DST are returned through the routine laboratory system and are used to guide clinical management where appropriate.

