### Outcome evaluation

To ascertain the primary and secondary outcomes, at enrolment all participants are allocated a review date 2 months from the enrolment visit. Participants are invited to attend clinic for review but are also invited to consent to telephonic follow-up and/or home visit in case clinic visit is not possible. Additional contact details are provided for at least one other family member (or other person designated by participant) at enrolment, wherever possible. Participants are told that, when attending the clinic for the follow-up visit, they will be reimbursed with a ZAR 50 grocery voucher (approximately equivalent to USD 6). Outcome data pertaining to TB treatment initiation, additional investigations, hospital attendances and admissions, and ART initiation (where appropriate) are collected on a case report form by the study nurse. In the event that no contact is made with patient or with named contact persons, follow-up information is collected from the clinic TB registers and the operational HIV programme database – permission to use these data is also included in the informed consent process.

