### Statistical analysis

Analysis of baseline characteristics will be performed to characterise the study population and to identify baseline imbalances between the study arms in order to decide whether any covariates need to be adjusted for in the final analyses. The baseline data will include: age, sex, body mass index (BMI), history of previous TB, HIV infection status, CD4+ cell count, and use of antiretroviral therapy and isoniazid preventive therapy.

All final analyses will be intention-to-treat analyses performed at the individual level taking account of within-cluster correlation. The definition of TB cases for the primary outcome will be based on MGIT culture positivity. The proportion of TB cases initiated on appropriate TB treatment within 30 days will be based on whether the appropriate treatment regimen was commenced within 30 days of the initial clinic visit—appropriate regimens are defined according to drug susceptibility pattern and with reference to national guidelines (Table 1) [27]. The primary analysis will include only TB cases not on TB treatment at the time of enrolment, i.e. excluding smear non-converters or failures still on treatment. The primary outcome is a binary variable (initiation of appropriate treatment or not) so univariate logistic regression will be performed as the primary analysis using generalised estimating equations (GEE) with a binomial distribution function and a logit link [28]. The odds ratio will be reported with 95% confidence intervals and a *p*-value from the Wald test. This method will allow for the correlation between observations (within clusters) without needing to specify a distributional assumption for the correlations. In addition, important individual-level characteristics that are unbalanced between arms will be included in the model as covariates. For the secondary outcomes with binary variables, GEE models will also be fitted with a binomial distribution function and a logit link. For the secondary outcomes with time-to-event measures, Cox proportional hazard models will be fitted with the shared frailty option to account for the cluster randomisation [29]. Hazard ratios will be presented with 95% confidence intervals.

**Table 1 T1:** Definitions of appropriate initial anti-TB drug regimen for primary outcome measurement

**Case definition***	**Appropriate initial anti-TB drug regimen**

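### The secondary objective names hospital admission, but the only hospital outcome listed is any hospital attendance, so no listed outcome answers that objective

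*Protocol article*

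**What the plan says.** The Background section of the protocol article gives as its first secondary objective the effect of positioning on "additional clinical outcomes (mortality, hospital admission, time to initiation of antiretroviral therapy". The list under Outcome measures covers mortality and time to ART. Its only hospital item is "Proportion of TB suspects and MDR-TB suspects with at least one hospital attendance within 60 days", which is not limited to admission, to unplanned care or to any reason for the visit.

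Under Outcome evaluation, "hospital attendances and admissions, and ART initiation (where appropriate) are collected on a case report form by the study nurse", so the two are named as separate data items. Table 2 in the Economic evaluation section likewise costs hospital admission and OPD attendance on separate lines.

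The Implementation section describes what happens after a negative Xpert result: antibiotics, advice to come back if there is no improvement after 14 days, and then "Patients who remain symptomatic following this course of antibiotics can be referred to the district hospital for chest X-ray and physician review". Rifampicin-resistant patients "are subsequently referred to the specialist drug-resistant TB treatment centre in Durban". The same pre-defined algorithms apply in both arms.

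On analysis, the Statistical analysis section says: "For the secondary outcomes with binary variables, GEE models will also be fitted with a binomial distribution function and a logit link".

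**The concern.** An objective needs an outcome that measures it. Here the objective asks about admission and the outcome counts attendance. A participant sent for a chest X-ray and one admitted as an emergency would each count as one event in the GEE model.

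The visits that separate the two definitions are partly a product of the trial's own diagnostic pathway. If the trial reports only attendance, it will not have answered its admission objective, and a difference in attendance could reflect more illness, more work-up, or both.

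**Working it through.** **1. Terms side by side**

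| Section of the protocol article | Term used |
|---|---|
| Background, secondary objectives | hospital admission |
| Outcome measures | at least one hospital attendance, 60 days |
| Outcome evaluation | attendances and admissions, both recorded |
| Economic evaluation, Table 2 | hospital admission and OPD attendance, separate lines |

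The last two rows rule out reading the terms as synonyms. No admission outcome is defined in the article. This step needs no assumption.

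**2. Do pathway visits meet the definition?** The article plans no figure for this outcome, so there is none to reproduce. A visit for X-ray and physician review at the district hospital is a hospital attendance, and nothing excludes it. Point-of-care results come on day 0 or 1, so referral could follow from about day 14 or 15. In the laboratory arm "participants are requested to return for results after 72 h", so referral could follow from about day 3 + 14 = 17. Both fall well inside 60 days. A shift of about three days therefore moves a 60-day proportion very little.

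**3. How many visits?** From Sample size: 1,664 participants, 25% expected culture-positive. Culture-negative: 1,664 × 0.75 = 1,248, most of whom would probably follow the Xpert-negative route. The article gives no referral rate. Assuming 10% to 20%: 1,248 × 0.10 = 125 and 1,248 × 0.20 = 250 visits, or 7.5% to 15.0% of all participants.

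**4. Effect on the odds ratio (illustration; all inputs assumed).** Let a be the probability of admission, R the share who receive their Xpert result, and r the probability of referral among those who do. Taking referral and admission as independent:

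P(attendance) = 1 − (1 − a)(1 − rR)

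With a = 10% (laboratory) and 8% (point of care), the admission odds ratio is (0.08/0.92)/(0.10/0.90) = 0.78. Worked case, r = 10% and R = 90% in both arms: 1 − 0.90 × 0.91 = 0.181 against 1 − 0.92 × 0.91 = 0.163, odds ratio 0.88. Attendance odds ratios over a range:

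| R, laboratory / point of care | r = 5% | 10% | 20% | 30% |
|---|---|---|---|---|
| 90% / 90% | 0.85 | 0.88 | 0.92 | 0.94 |
| 85% / 95% | 0.88 | 0.94 | 1.01 | 1.06 |
| 70% / 95% | 0.93 | 1.03 | 1.17 | 1.28 |

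With admission at 15% against 12% (odds ratio 0.77), the three rows run 0.82 to 0.91, 0.84 to 1.02 and 0.88 to 1.20.

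**5. When does the sign reverse?** With equal receipt it never does; the effect is only diluted. For 85% / 95%, setting the arms equal gives 0.90(1 − 0.85r) = 0.92(1 − 0.95r), so 0.109r = 0.02 and r = 18%. At average receipt of 90% that is 0.1835 × 0.90 = 16.5% of all participants, just above the range in step 3. For 70% / 95%, 0.244r = 0.02 and r = 8%, but the 25-point gap in receipt is itself invented for the illustration.

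**The case against.** The strongest defence is that attendance is a legitimate outcome in a pragmatic comparison of strategies. Referrals that a strategy generates are part of its effect, and the article nowhere says that attendance is a bad outcome. Admissions are recorded too, so attendance can be read beside them. A working definition of attendance may also sit in the full protocol, which is not shown.

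Much of this stands. Attendance is a sensible resource-use measure, and the missing working definition is no finding. But condensing a protocol does not explain naming one endpoint in the objective and a different one in the outcome list when the article elsewhere keeps the two apart. Recording admissions does not make them a listed outcome.

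A reader might go further and infer that pathway referrals are scored as failures, so that faster work-up at the clinic will look like harm. The documents do not support that. No direction of benefit is set for this outcome, the referral rules are the same in both arms, and the timing difference is about three days. Reversal needs more point-of-care participants to receive a result and be referred. The Discussion plans to examine the proportion returning for results but gives no figure.

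Nor can the drug-resistant referrals be counted with confidence. At least 10% MDR-TB among 2 × 208 = 416 culture-positive cases would be about 42 people, but the Durban centre is not expressly called a hospital.

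**Conclusion.** The point holds as an inconsistency between objective and outcome: admission is the stated objective, attendance is the only hospital outcome, and the article itself distinguishes them. That conclusion rests on the text alone.

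The further point, that pathway visits can dilute an admission difference and blur the attendance result, follows from the text in kind but not in size. The odds ratio range of 0.85 to 0.94 against 0.78 assumes 10% against 8% admission, 5% to 30% referral and 90% receipt in each arm. A reversed sign is an edge case on inputs the article does not supply, and should not be presented as the expected result.

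One secondary outcome is affected. The primary outcome, its analysis and the sample size are not. It should be corrected because the correction is cheap.

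**What to change.** Reconcile the secondary objectives in Background with the list under Outcome measures. List at least one hospital admission within 60 days as the secondary outcome, analysed with the binomial GEE model with logit link already planned for binary secondary outcomes. Report at least one hospital attendance separately, labelled as resource use. Enrolment began on 22 August 2011, so document this as a change made after that date, with the reason.

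Do not remove visits according to why the participant was referred. That would condition on a reason arising after randomisation and judged by unblinded staff: the study nurse makes the clinical decisions and also collects the outcome data. The article does not say that the reason for a visit is recorded.

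**Cost.** No new data collection, since both items are named for the case report form. There will be fewer events and a wider confidence interval for this odds ratio. That need not mean less power for an admission difference. Under the 10% against 8% illustration, with 16 clusters per arm of 1,664/32 = 52 participants, κ = 0.05 and no loss to follow-up, the Hayes and Bennett formula gives power of about 28% on admission. With 90% receipt in both arms, power on attendance is 9% to 20%. Either way, the result for this outcome should be read as an estimate with its interval.
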